### Sample size

Although there is a lack of evidence-based guidance for the optimal sample size for each group participating in the Delphi survey, we aim to recruit a minimum of 180 participants overall (minimum of 30 per each of three major stakeholder group categories, i.e. parents/caregivers whose infants have been diagnosed with or treated for neonatal encephalopathy, healthcare providers and researchers with expertise in neonatal encephalopathy treatment) for each Delphi survey (i.e. 90 participants in the Multi-Round Delphi survey and 90 participants in the Real-Time Delphi survey) and retain participants using the retention methods as described.

### Data collection methods

This trial involves the use of an online survey (questionnaire) tool using Calibrum (Surveylet).

In the Multi-Round Delphi arm, participants must complete all rounds of the Delphi for their rating to be counted and to influence the outcomes emerging from the Delphi and moving forward to the consensus meeting(s) (Phase 4). In the Real-Time Delphi arm, participants must rate an outcome at least twice for their rating score to be counted. The Delphi surveys will aim to follow the timeline as outlined in Fig. 2. However, the process may be iterative, and timelines may be adjusted.

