#### Real-Time Delphi method

The Real-Time Delphi survey will contain outcomes identified from a systematic review of (1) randomised trials and (2) systematic reviews of randomised trials, of interventions for the treatment of neonatal encephalopathy. In addition, outcomes identified as important to parents/caregivers of infants who have been diagnosed with and received treatment for neonatal encephalopathy identified through one-to-one interviews will be included. The survey will also include a short questionnaire seeking participant demographic information.

Participants will be asked to rate the importance of each outcome for inclusion in the COS using a 9-point Likert scale used commonly in the Delphi method for COS development [4]. For each outcome, the participant will be able to view how they rated each outcome, the overall rating results for each outcome and the results for each outcome from each stakeholder group, in real-time. This information will be displayed as feedback immediately after a participant rates an outcome for the first time. With this feedback, participants will be able to modify their answer or keep it the same before moving on to the next outcome. Participants will be encouraged to suggest additional outcomes that they feel are omitted from the list of outcomes presented in the survey. Additional outcomes will be reviewed within 2 days by a representative subgroup from the COHESION Steering Group (i.e. parents/caregivers, healthcare providers and researchers) and included in the Real-Time Delphi survey, if not already captured in the outcomes list. As the degree of consensus changes, depending on how participants rate an outcome, we will encourage participants to re-visit the survey and review their answers based on the degree of consensus. If a participant scores 6 or more points different on the 9-point scale from that given by overall group consensus score (e.g. if the overall group consensus is that an outcome is extremely important and ranks 9 on the Likert scale, and the participant rates it extremely unimportant, as 1 on the Likert scale and vice versa), they will be given the option to comment on the reasoning behind the rating they have given. Participants can save and re-visit the survey to complete the questions and/or modify their answers.

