#### Secondary outcomes

We will compare the outcomes that are prioritised (based on Table 1), from each survey arm, against the final COS.

Additional secondary outcomes are informed by previous comparison of Multi-Round Delphi method and the Real-Time Delphi method by Gnatzy et al. [8]:
2.*Feedback effect*

We will calculate the “feedback effect”, which will inform if, and how, the feedback provided to participants resulted in them amending how they rated an outcome. In the Multi-Round Delphi, participants will be given time (1 week) to process the feedback before the next round, where they can re-rate the outcomes. In contrast, in the Real-Time Delphi, participants will be provided with feedback in real-time. They will be given the option to change their rating or keep their answer the same before moving on to the next outcome. To estimate the feedback effect, we will test the null hypothesis:H0_1_: There is no difference in how participants react to feedback in both survey arms

We will use the following model to estimate this effect:
$$ {cor}_{kl}={b}_o+{b}_1\ast {dev}_{kl}+{b}_2\ast \gamma k+{b}_3\ast \left(\gamma k\ast {dev}_{kl}\right) $$*k*: participants of both Multi-Round and RT Delphi surveys*l*_s_: the projection dependent on *s* which indicates whether the projections (outcome rating) are from the Real-Time (*s* = 1) or Multi-Round (*s* = 2) Delphi study.cor_*kl*_ will indicate how strongly the *expected-probability (EP) values* were corrected after feedback was given.Dev_*kl*_: how strongly a stakeholder deviated from the final expected-probability value.γk∈{0, 1}: an indicator variable which takes on the value 1 if the expert *k* belongs to the Real-Time and 0 if an expert belongs to the Multi-Round Delphi study.*b*_1_: slope coefficient*b*_2_: indictor variable*b*_3_: interaction term3.*Initial condition effect*

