To ensure that the first participant of the Real-Time Delphi survey is provided with feedback, a representative group of stakeholders (five of each parents/carers, healthcare providers and researchers) will vote on the importance of the outcomes (i.e. “initial conditions”) before the survey goes live to the public. These “initial conditions” may have an impact on how outcomes are rated subsequently during the survey process; we call this the “initial condition” effect. In addition, it may be suggested that participants engaging later in the survey have a greater level of feedback than early participants. This might influence how outcomes are re-rated. To identify if the initial conditions effect the final list of outcomes, we will test the hypothesis:H0_2_: There is no effect of the initial conditions on the outcomes that emerge as important at the end of the Delphi survey.

We will conduct a regression analysis with initial conditions and final results. The initial conditions will be the independent variable and final results will be the dependent variable. Furthermore, we will test whether the initial conditions cause participants to change their rating on outcomes compared to late participants. For this, we will use a linear regression model.
$$ {\mathrm{cor}}_{ij}={\beta}_0+{\beta}_1\ast {\mathrm{dev}}_{ij}+\beta 2\ast {\upvarphi}_i+{\beta}_3\ast \left({\upvarphi}_i\ast {\mathrm{dev}}_{ij}\right) $$*i*: participants in the Real-Time Delphi survey*j*: the projection (outcome rating)cor_*ij*_: how strongly the stakeholder’s *EP* assessment was altered after proving feedbackdev_*ij*_: how strongly a stakeholder differed from their *EP* valueφ_i_ ∈{0,1} represents an indicator variable where the value is 1 if the stakeholder *i* is an early participant (week 1) or 0 if the stakeholder is a late participant (week 4).

This model was developed by Gnatzy et al. [8] predicts how the deviation from average EP impacts corrections whilst accounting for possible differences between early and late respondents.
4.*Iteration effect*

In a Multi-Round Delphi survey, participants can only re-rate the outcomes in the second and third rounds. However, in the Real-Time Delphi, participants have the opportunity to re-visit the survey and re-rate the outcomes as many time as they wish. This difference in the iteration (“iteration effect”) could impact the consensus process.

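### The Real-Time arm lets participants keep a rating after feedback but counts only outcomes rated at least twice, and does not say whether a kept rating is a second rating

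*Protocol article*

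**What the plan says.** All references are to the protocol article.

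- **Response to feedback, Real-Time arm** (Real-Time Delphi method): feedback appears once an outcome has received its initial rating. "With this feedback, participants will be able to modify their answer or keep it the same before moving on to the next outcome". The feedback-effect text under Secondary outcomes repeats this: "They will be given the option to change their rating or keep their answer the same before moving on to the next outcome".
- **Counting rule, Real-Time arm** (Data collection methods): "participants must rate an outcome at least twice for their rating score to be counted".
- **Counting rule, Multi-Round arm** (same section): "In the Multi-Round Delphi arm, participants must complete all rounds of the Delphi for their rating to be counted". The sentence goes on to tie counting to the outcomes that emerge and go to the consensus meetings.
- **Later visits, Real-Time arm**: "Participants can save and re-visit the survey to complete the questions and/or modify their answers" (Real-Time Delphi method), and "participants have the opportunity to re-visit the survey and re-rate the outcomes as many time as they wish" (Secondary outcomes, iteration effect).
- **Use of the ratings**: the primary outcome compares the lists and their Table 1 classification, which rests on percentages of participants. H0_1 states that reaction to feedback does not differ between arms. It is examined by regressing the correction (cor) on the deviation (dev), an arm indicator and their interaction, with coefficients b1, b2 and b3.

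**The concern.** Keeping a rating after seeing the feedback is offered as a complete response, and the participant then goes on to the next outcome. The counting rule asks for two ratings of the outcome. The two provisions are not reconciled, and two teams following this text could build different datasets.

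If a kept rating is not a second rating, the rule selects on the reaction to feedback, and it does so in one arm only. A Real-Time participant who changes in a single pass has two ratings and counts. One who considers the feedback and stands by the score has one rating and does not count. In Multi-Round the condition is completion of the rounds, so an unchanged score counts and is a correction of zero.

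Two analyses are exposed. The Real-Time Table 1 percentages would over-represent people who changed their rating, whichever data the regression uses. The feedback model would lose zeros from one arm, if the counting rule also defines its data. The early/late model under the initial condition effect uses the same kind of correction and inherits the same question.

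**Working it through.** **The plan's own figures.** The protocol gives no rate of change after feedback, so it has no figure on this point to reproduce. The sample size is consistent: 2 arms × 3 stakeholder groups × 30 = 180.

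**Set-up.** Let q be the probability that a rating is changed after feedback. Let r be the probability that a kept rating still yields a countable second rating, either because the keep is stored as one or because the participant returns and re-enters the score. Behaviour is identical in both arms, so the true b3 is 0.

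**Who is counted in Real-Time.** The share of ratings counted is q + (1 − q)r. The share of changers among them is q / [q + (1 − q)r]. At q = 0.2 that share is:
- r = 0: 0.2/0.2 = 100%
- r = 0.5: 0.2/0.6 = 33%
- r = 1: 0.2/1 = 20%, the true rate

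**Effect on the slope.** With signed deviations centred near zero, the slope of cor on dev is Σ(dev·cor)/Σ(dev²). Rows with cor = 0 add nothing to the numerator, so dropping them only shrinks the denominator and a positive slope rises. If changing does not depend on dev, the Real-Time slope is multiplied by 1/[q + (1 − q)r]:
- r = 0: 1/0.1 = 10 at q = 0.1, and 1/0.5 = 2 at q = 0.5
- r = 0.5: 1/0.55 = 1.82 at q = 0.1, and 1/0.75 = 1.33 at q = 0.5
- r = 1: 1.0 throughout

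**Simulation check.** Assumptions not in the protocol: 50 outcomes, SD of dev 1.8, slope 0.5 among changers, noise SD 0.5, q from 0.1 to 0.5, 20 runs per setting. The 90 per arm is the protocol's figure. In the second block the chance of changing rises with |dev|. Cells show the ratio of Real-Time to Multi-Round slope, with the spurious b3 in brackets.

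| Changing depends on dev? | q | r = 0 | r = 0.5 | r = 1 |
|---|---|---|---|---|
| No | 0.1 | 10.44 (0.459) | 1.86 (0.043) | 1.03 (0.001) |
| No | 0.2 | 4.91 (0.399) | 1.67 (0.067) | 1.02 (0.002) |
| No | 0.3 | 3.38 (0.353) | 1.53 (0.079) | 0.99 (−0.001) |
| No | 0.5 | 2.01 (0.252) | 1.34 (0.084) | 1.00 (0.000) |
| Yes | 0.1 | 5.01 (0.401) | 1.67 (0.068) | 1.01 (0.001) |
| Yes | 0.2 | 2.51 (0.301) | 1.41 (0.084) | 0.99 (−0.002) |
| Yes | 0.3 | 1.70 (0.206) | 1.26 (0.078) | 0.99 (−0.002) |
| Yes | 0.5 | 1.21 (0.085) | 1.09 (0.039) | 1.00 (−0.001) |

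The mean absolute correction moves the same way: at q = 0.2, r = 0 and changing independent of dev, it is 0.17 in Multi-Round and 0.83 in Real-Time. Where corrections are analysed as magnitudes, b2 could be affected as well as b3; b2 was not estimated separately.

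**The case against.** A reader might infer that no change cannot be recorded at all in the Real-Time arm, and that its feedback effect is therefore inflated by construction. The protocol does not support that, for four reasons.

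- The rule asks for two ratings, not two different ones. Re-visits are allowed without limit, and a score re-entered unchanged satisfies the rule with a correction of zero.
- The text does not say how the platform stores a kept rating. Feedback follows the first rating, so the change-or-keep step could be meant as the second. On that reading there is no bias, and a rule that then excludes few people is not an error.
- Counting is explained, in the parallel Multi-Round sentence, by reference to the outcomes that emerge. The feedback model does not cite the rule, and the choice of rows for a secondary regression may be settled in a document not shown.
- Deleting every zero from one arm must produce an arm difference. The r = 0 column is a worst case, not evidence that H0_1 would be rejected.

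All four stand as limits on the claim. They do not remove the conflict. The rule is stated in the protocol, and its plain wording treats one-pass changers and one-pass keepers differently. The effect on who is counted in Table 1 does not depend on the regression. If the platform does not store a kept rating, the information may not be recoverable later.

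**Conclusion.** The point holds as an unreconciled conflict between the response options and the counting rule, with a conditional risk of bias. On the literal reading, unchanged ratings are under-recorded in Real-Time only. That over-represents changers in the percentages behind the primary outcome. No shift in any Table 1 classification was computed, so its practical effect there is unknown.

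For H0_1, upward bias requires two things that the protocol leaves open: that some kept ratings are not counted (r < 1), and that the counting rule selects the data for the feedback model. Given both, the Real-Time slope is inflated about 1.2- to 10-fold if no kept rating counts. If half count, the factor is 1.3 to 1.8 when changing is unrelated to deviation and 1.1 to 1.7 when it is related. If all count, there is no inflation. These factors rest on assumed change rates of 0.1 to 0.5. A built-in bias of known size, or certain rejection of H0_1, goes beyond what the text supports.

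**What to change.** Under Data collection methods, state that a Real-Time rating counts once the feedback for that outcome has been shown and the participant has changed or kept the rating, with a kept rating stored as a second rating equal to the first. Under Secondary outcomes, include these ratings with cor = 0, and state that the feedback and early/late models use all ratings made before and after feedback.

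The cost is a few sentences and a platform setting that records the keep action. No extra participants are needed, and Trial status says that recruitment has not begun.

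The downside is that one-pass raters then count. If two separate visits were intended, the protocol should say so and apply the requirement equally to changers and keepers, with kept ratings still included in the feedback model.

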### Data monitoring

A Data Monitoring Committee is not needed in this study. Steering Group members for COHESION are responsible for trial governance and will monitor outputs continuously from the Delphi processes and pay close attention to retention within the trial and ensure reminder emails are employed to tackle this. Monitoring the data will not influence the participants within their intervention; it will only ensure target sample sizes are achieved.

### Protection of human participants

The COHESION project has received ethical approval from the National University of Ireland, Galway (approval reference: 19-Apr-14). Consent will be obtained from participants and they will retain the right to withdraw from the study at any point. Participants will have up to 1 week to consent but may choose to consent more quickly. We will track participant responses using their name and email addresses. However, all responses will remain confidential and individual names will not be linked directly to individual responses in any reports at any time during or after the study. The web-based system Calibrum (Surveylet) that will be hosting the survey will maintain data behind a firewall accessible only by the researchers who must provide passwords and user-IDs. In addition, all data will be analysed according to groups rather than by individual person.

## Dissemination of findings

Findings from the trial will be communicated to all participants of the trial by email. The results of the trial will be disseminated to stakeholders through channels that were used for recruitment, conference presentations and journal papers.

## Trial status

Protocol version 1 (01/09/20). Participant recruitment has not yet commenced. Recruitment will be completed by 01/09/21.

## Data Availability

All datasets used and/or analysed during the COHESION study will be held by COHESION team as [contact].

## Abbreviations

COS: Core outcome set
COHESION: Core Outcomes in Neonatal Encephalopathy
SPIRIT: Standard Protocol Items: Recommendations for Interventional Trials
USE: Usefulness, Satisfaction, Ease of Use
GDPR: General Data Protection Regulation
SD: Standard deviation
EP: Expected probability
